### The expected results

Concerning the study 1, the main results to be expected are that a different and reduced C (*C* < 0) and (ß < 1) are expected in currently-ill AN and BN patients compared to non-ED underweight, normal-weight and illness-recovered controls, and during a swallowing compared with a sip-and-spit condition. Reduced C and ß-values would show a response bias to say, “Yes, the gaining weight-related attribute [sweetness, creaminess and caloric content] is present.” By contrast, patients will have a similar high d′ value compared with control groups, which means that all the participants have a good sensory discrimination.

Concerning the study 2, it is mainly predicted that restricting-type AN will show evidence of reduced verbal ratings as well as bodily higher corrugator activity, disgust facial expressions and heart rate acceleration in response to high-sweet and high-fat foods compared to stimuli of low-sweet and low-fat foods; non-ED underweight, normal-weight, illness-recovered controls and BN patients; and especially during the swallowing compared with the sip-and-spit condition. On the other hand, higher zygomatic muscle activity and more smiles expressions in response to very sweet tastes will be expected to observe in BN compared to fat and low-sweet stimuli; non-ED underweight, normal-weight, illness-recovered controls and restrictive-type AN; and no differences between swallowing and sip-and-spit conditions.

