H1: If perceptual disturbances in AN and BN are related to biased cognitions about gaining weight rather than to gustatory deficits or BMI, then AN and BN patients should respond with similar sensory performance but higher response bias scores in a discrimination test, (1) compared to non-ED underweight, normal-weight and illness-recovered controls, and (2) during a swallowing compared with a sip-and-spit condition.H2: If fear of weight-gain in restricting-type AN elicits taste aversion, then facial electromyographical, facial expression, and autonomic and subjective correlates of disgust (Kappas, 2003; Kreibig, 2010) while tasting high-sweet and high-fat foods should be observed compared to (1) stimuli of low-sweet and low-fat foods; (2) non-ED underweight, normal-weight, illness-recovered controls and (3) BN patients; and (4) especially during the swallowing compared with the sip-and-spit condition.H3: If avoidance of energy-rich foods in BN reflects a cognitive preoccupation about the increased liking of very sweet tastes associated with gaining weight, then facial electromyographical, facial expression, and autonomic and subjective correlates of pleasure (Kappas, 2003; Kreibig, 2010) while tasting high-sweet foods should be observed compared to (1) fat and low-sweet stimuli; (2) non-ED underweight, normal-weight, illness-recovered controls and (3) restrictive-type AN; and (4) no differences between swallowing and sip-and-spit conditions.

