	**Ratings**: sweetness and fattiness identity and intensity (score) **SDT parameters**: d′ (sensory sensitiviy), C and ß (response bias based on cognitive strategy)	11-point anchored Likert-type scale (scores from 0 to 10) designed to measure taste perception	Sussex Ingestion Pattern Monitor (SIPM™ 2.0); Sussex University; UK	Primary	Study 1
	**Ratings**: pleasantness of the taste (score)/thirst and hunger level (score)/familiarity of food samples.	Time-intensity measures for pleasure; opportunity to scale the perceived liking dynamically over 60 sec. Labeled magnitude scale for thirst/hunger	SensoMaker™; UFLA, Brazil	Primary/secondary	Study 1 & 2
Behavioural	**Facial expressions**: general emotions, valence and actions units (intensity score)	Positive/negative valence as measure of overall affection; general emotions (joy, anger, surprise, fear, contempt, sadness, disgust); action units as the likelihood of specific facial muscle activations	FACET™ SDK; iMotions Inc., Cambridge Innovation Center, US	Primary	Study 1 & 2
Psycho-physiological	**Cardiovascular**: heart rate and heart rate variability	Cardiovascular Changes as index of cardiac sympathetic activation and autonomic arousal	Module—GSR & Heart Rate and ECG/EMG; Shimmer3 EMG/ECG, GSR Kit and EXG Devices; iMotions Inc., Cambridge Innovation Center, US	Primary	Study 2
	**Electrodermal activity**: skin conductance level (μmhos), skin conductance response rate (count/min)	Changes in the conductivity of skin as index of sympathetic activation		Primary	Study 2
	**Facial electromyography**: EMG powers (mV)	EMG activity of the levator labii (disgust), corrugator supercilia (general negative affect) and zygomatic major (pleasure) muscle regions		Primary	Study 2

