### Safety aspects

Adverse events are not expected and the planned measures for collecting personal data entail only minimal risks and burden. In particular, the present research collects data without using invasive behavioral or physiological procedures. Nevertheless, potential inconveniences due to using video recordings in this clinical sample will be properly addressed following current guidelines and recommendations (General Medical Council, 2002; Parry et al., 2016). As being video-recorded can raise anxieties and concerns and, therefore, can constitute an additional burden for patients, our research will provide several strategies ensuring video recordings are made in minimally intrusive ways: (1) we will reduce the intrusiveness of being filmed by using the laptop's inbuilt webcam, (2) researchers will not be in the same room during testing, and (3) a period of habituation to being filmed during the training session. For those participants who do not agree to be filmed, only facial electromyography recordings will provide measures of the hedonic reactions. Otherwise, hedonic reactions will be measured by facial expressions and facial electromyography only (to improve validity and reliability of hedonic assessment and enhance observations of small/subtle but meaningful emotional changes). Finally, during food tasting there will be more degustation than during a typical meal and thus the participants should consume only a small amount of chocolate ice cream in the swallowed condition, while they are requested to expectorate the food samples after assessing them in the spit condition. Doing so, this set-up is expected to reduce the inconveniences due to the fear of weight gain, especially in patients. Nevertheless, any aggravation of symptoms even when not related to the experimental procedure will be documented at every assessment throughout the study procedure. Finally, based on our previous experience with psychological and psychophysiological measures-related projects with EDs (e.g., Vögele and Florin, 1997; Vögele et al., 2009; Munsch, 2014), a framework for considering possible risks to participants' privacy, dignity and safety in all phases, and for planning measures that can reduce those risks is guaranteed.

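### The only EMG sign predicted for H2 is corrugator activity, which Table 2 defines as general negative affect; levator labii, the muscle it assigns to disgust, is missing from the prediction

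*Protocol article*

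**What the plan says.** All references are to the protocol article.

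- **Hypothesis section, H2.** If fear of weight gain produces taste aversion in restricting-type AN, the study should observe "facial electromyographical, facial expression, and autonomic and subjective correlates of disgust" on tasting high-sweet and high-fat foods. The comparisons are with low-sweet and low-fat stimuli, the control and recovered groups, and BN, with the effect strongest on swallowing.
- **Table 2, facial electromyography (a primary outcome of Study 2).** Three sites are recorded, each with its own meaning: "EMG activity of the levator labii (disgust), corrugator supercilia (general negative affect) and zygomatic major (pleasure) muscle regions".
- **Table 2, facial expressions.** The software scores "general emotions (joy, anger, surprise, fear, contempt, sadness, disgust" as separate emotions, so disgust and fear are distinguished.
- **Table 2, cardiovascular measures.** These are described as "Cardiovascular Changes as index of cardiac sympathetic activation and autonomic arousal".
- **The expected results, Study 2.** For restricting-type AN: lower verbal ratings and "bodily higher corrugator activity, disgust facial expressions and heart rate acceleration in response to high-sweet and high-fat foods". For BN: "higher zygomatic muscle activity and more smiles expressions in response to very sweet tastes".
- **Planned analysis.** All facial EMG outcomes enter mixed three-way ANOVAs. No muscle is singled out for any hypothesis.
- **Safety aspects.** "For those participants who do not agree to be filmed, only facial electromyography recordings will provide measures of the hedonic reactions".

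**The concern.** H2 is a claim about disgust, not about negative feeling in general. The article records a muscle that it labels as the disgust muscle, yet the expected result for H2 names a different one, which it labels as non-specific. Levator labii appears only in Table 2.

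The distinction matters to the article's own model. Figure 1 describes two steps in restricting-type AN: thoughts about weight make eating feel bad, and that feeling then spreads to the taste itself. On Table 2's labels, corrugator can show the first step, and levator labii is the EMG measure of the second. The Discussion makes the inference of a hedonic shift towards disgust depend on the current predictions being confirmed. If the listed prediction contains the non-specific muscle and omits the specific one, the EMG part can be confirmed without bearing on disgust.

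**Working it through.** No arithmetic beyond a count applies. The check sets the hypothesis, the definitions of the measures and the predicted result side by side.

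**Step 1: does the predicted muscle match the construct?**

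| Hypothesis | Construct | Muscle for it in Table 2 | Muscle in the expected results | Match |
|---|---|---|---|---|
| H2 (AN) | disgust | levator labii | corrugator | no |
| H3 (BN) | pleasure | zygomatic major | zygomatic | yes |

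The H3 row shows that the article does map muscle to construct in this section. The mapping fails for H2 only.

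**Step 2: how specific is each sign predicted for H2, by the article's own labels?**

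| Predicted sign | What Table 2 says it measures | Specific to disgust? |
|---|---|---|
| Lower ratings | pleasantness of the taste | no |
| Higher corrugator | general negative affect | no |
| Disgust facial expression | disgust, scored apart from fear | yes |
| Faster heart rate | sympathetic activation and arousal | no |

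The count is 1 of 4 in filmed participants. Without film the facial-expression row drops out, leaving 0 of 3.

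**Step 3: is the disgust muscle measured and analysed?** Yes. Levator labii is part of facial EMG, a primary outcome of Study 2. The ANOVAs cover the EMG outcomes without excluding any muscle, and nothing ties EMG recording to consent to filming. Adding levator labii to the prediction would give 2 of 5 specific signs in filmed women and 1 of 4 in unfilmed women.

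**Step 4: how many women are affected by the filming point?** The article gives no refusal rate. The sample-size section plans 15 currently ill AN participants per study, so the number without a disgust-specific predicted sign could lie anywhere from 0 to 15 in that group. The mismatch in Step 1 does not depend on this number.

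**Step 5: is there a rule for combining the signs?** None is stated. The article does not say whether all the predicted signs must appear, or how a mixed result would be reported, for example corrugator and heart rate raised while levator labii and disgust expression stay flat.

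**The case against.** The strongest reply is that the expected-results section is a short list of main predictions, not an endpoint definition. H2 itself asks for EMG correlates of disgust, and read with Table 2 that already points to levator labii. The muscle is recorded, belongs to a primary outcome and is analysed. The predicted list is joined by *and*, and it includes a disgust-specific expression. All of this stands. It limits the point to the stated prediction and its interpretation. It does not remove the disagreement between two things the article does state, so this is not merely detail left to a fuller document.

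A reader might infer three stronger claims, which the documents do not support:

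- **That fear of weight gain could pass as disgust, so the trial could declare taste aversion from anxiety alone.** In filmed women, fear without a disgust expression would not meet the stated prediction, and no rule says that corrugator or heart rate suffices. Fear of weight gain is also H2's proposed cause of the aversion, not a rival explanation, and a stronger response on swallowing is part of the hypothesis. Table 2 shows that the other signs are non-specific; it does not say that anxiety would produce them. H2 cites outside sources for its disgust correlates, and what they list cannot be judged here.
- **That EMG is the only objective measure in unfilmed women.** The safety section limits its statement to measures of hedonic reactions. Cardiovascular and electrodermal measures are separate primary outcomes and are not tied to filming.
- **That levator labii must be the single deciding outcome for H2.** The facial-expression score is also disgust-specific, so the defect does not require this.

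**Conclusion.** The point holds as a mismatch between the Study 2 prediction for H2 and the article's own definition of its measures. The only EMG sign predicted for a disgust hypothesis is the one labelled as general negative affect, and the muscle labelled as disgust is left out. One of four predicted signs is disgust-specific in filmed participants, and none of three in those who decline filming.

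The size is modest. No measurement, variable or model changes, and no error rate or power figure is affected. What is at stake is how specific a positive H2 conclusion would be, chiefly under a mixed pattern of signs and in unfilmed women, whose number is unknown. The verdict takes Table 2's labels for the muscles and other measures at face value and uses no outside evidence on what each one indicates.

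**What to change.** In the expected-results section for Study 2:

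1. Add higher levator labii activity as the predicted EMG sign of disgust for H2, in the contrasts that H2 already lists.
2. Keep corrugator activity, heart rate acceleration and lower ratings, described as supportive but non-specific signs of negative affect or arousal.
3. State that disgust or taste aversion will be concluded only when a disgust-specific sign is raised: levator labii EMG or, where filmed, the facial-expression disgust score. Raised non-specific signs alone would be reported as negative affect or arousal.

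The H3 prediction needs no change on this point. The cost is a few sentences, since levator labii is already recorded and no new data are needed. The downside is a slightly stricter bar for claiming H2. The wording should be settled before Study 2 outcome data are examined, so that the choice of muscle cannot follow the results.

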### Safety aspects

Adverse events are not expected and the planned measures for collecting personal data entail only minimal risks and burden. In particular, the present research collects data without using invasive behavioral or physiological procedures. Nevertheless, potential inconveniences due to using video recordings in this clinical sample will be properly addressed following current guidelines and recommendations (General Medical Council, 2002; Parry et al., 2016). As being video-recorded can raise anxieties and concerns and, therefore, can constitute an additional burden for patients, our research will provide several strategies ensuring video recordings are made in minimally intrusive ways: (1) we will reduce the intrusiveness of being filmed by using the laptop's inbuilt webcam, (2) researchers will not be in the same room during testing, and (3) a period of habituation to being filmed during the training session. For those participants who do not agree to be filmed, only facial electromyography recordings will provide measures of the hedonic reactions. Otherwise, hedonic reactions will be measured by facial expressions and facial electromyography only (to improve validity and reliability of hedonic assessment and enhance observations of small/subtle but meaningful emotional changes). Finally, during food tasting there will be more degustation than during a typical meal and thus the participants should consume only a small amount of chocolate ice cream in the swallowed condition, while they are requested to expectorate the food samples after assessing them in the spit condition. Doing so, this set-up is expected to reduce the inconveniences due to the fear of weight gain, especially in patients. Nevertheless, any aggravation of symptoms even when not related to the experimental procedure will be documented at every assessment throughout the study procedure. Finally, based on our previous experience with psychological and psychophysiological measures-related projects with EDs (e.g., Vögele and Florin, 1997; Vögele et al., 2009; Munsch, 2014), a framework for considering possible risks to participants' privacy, dignity and safety in all phases, and for planning measures that can reduce those risks is guaranteed.

## Discussion

Determining how food is actually perceived in patients with AN and BN is of crucial importance. First, if the current predictions are confirmed, restricting energy intake in AN might also be motivated by hedonic shifts, in which palatable food changes from a liked to a disliked or even disgusted entity. A better understanding of the conditions under which food becomes disgusting should help to explain why AN patients select and avoid certain foods and how they lose their appetite. Furthermore, additional knowledge on cognitive mechanisms in the top-down process of taste hedonics complements theoretical models and fosters the specificity of new cognitive interventions reducing taste aversions. Second, to the extent that taste aversions seem to be crucial in the trajectory and treatment of other forms of anorexia such as avoidant/restrictive food intake disorder (ARFID), vagotomy surgery- or cancer-induced anorexia (Bernstein and Borson, 1986; Hildebrandt et al., 2015), added knowledge on the development of aversions to dietary items might help to identify new targets in the prevention and treatment of at individuals at risk and people with AN or the taste characteristics of food-based ARFID (e.g., using flavor-pre-exposure procedures). Likewise, food learning techniques might be used for the acquisition of new functional food preferences (e.g., via conditioned-flavor learning) to overcome taste aversions in anorectics, and for the devaluation of the increased hedonic impact of sweet cravings and binge-eating in BN (e.g., via food-devaluation procedures). Third, exact knowledge about whether avoidance of high-caloric food is based on unpleasant taste responses or intentional actions to prevent weight gain, will shed light on previously neglected mechanisms related to the development of EDs. Moreover, future studies might investigate whether taste responsiveness represents a stable or variable marker of different types of EDs over time.

Interestingly, although dietary learning-based procedures have not been tested yet in patients with EDs, they have been successfully used in animal models and non-eating disordered human studies in an attempt to prevent, modify and reduce gustatory aversive associations and the hedonic impact of food stimuli. For instance, procedures to develop learned preferences for distasteful flavors are well-established in animal models (e.g., González et al., 2010). By contrast, well-known procedures that may reduce the effectiveness of and limit learning about the hedonic food reward concern flavor extinction (e.g., Garcia-Burgos and González, 2012), flavor pre-exposure (e.g., Garcia-Burgos et al., 2013), and blocking of flavor learning (e.g., González et al., 2014). In human studies, for instance, counter-conditioning and extinction interventions have been recently applied to target affective conditioning characteristic of disgust (e.g., Klucke et al., 2013; Hildebrandt et al., 2015). Moreover, food-devaluation procedures are currently being used to test behavioral sensitivity to reward in populations with weight problems (e.g., Horstmann et al., 2015). Therefore, evidence of disgust reactions in AN would raise some important possibilities for future research and development of clinical interventions, and the applications of dietary-learning for therapy appear to be promising as we move toward a more comprehensive understanding of the learning principles that affect EDs.

## Availability of data and materials

The dataset that will be analyzed during the current study will be available from the corresponding author on reasonable request. There will be no personal identification of participants in the data set.

## Abbreviations

AN: Anorexia Nervosa
ANOVA: analysis of variance
BDI-II: Beck Depression Inventory-II
BMI: Body Mass Index
BMS: Brief Mood Scale questionnaire
BN: Bulimia Nervosa
C-AN: currently ill anorectic
C-BN: currently ill bulimic
DIPS: Diagnostic interview for psychiatric disorders
ED: Eating Disorders
EDE-Q: Eating Disorder Examination Questionnaire
EMG: Electromyography
FCQ-T-reduced: Food Cravings Questionnaire—Trait
MSTL: Multiple-Sip Temporal-Liking
N-CT: normal weight control
R-AN: recovered anorectic
R-BN: recovered bulimic
SCID-I: Structured Clinical Interview for DSM-IV
SDT: Signal Detection Theory
T-I: Time-Intensity
TR: Taste Reactivity
TSF-B: Thought-Shape Fusion Body State Scale
TSF-Trait: Thought-Shape Fusion Trait Questionnaire
U-CT: underweight control.
